##### Cost and healthcare utilization

The Micro-costing Questionnaire will be used to collect data from the expense report, including cost-generating events not directly linked to a specific patient, to calculate total labor expenses (e.g., training costs), and non-labor expenses (e.g., supplies, educational materials, and administrative overhead) utilized by each group in the study. Cost-generating events will include (1) training providers to promote behavioral change, (2) distributing DSTs and educational materials, (3) providing continued technical support to providers and patients in text messaging use, and (4) administrative overhead for FQHCs, if applicable. The Health Services Utilization Form was developed and tested in a prior trial and captures health services utilization and patient out-of-pocket expense [78]. It gathers self-reported number of times the patient visits a specialist (e.g., dietitian, cardiologist), emergency room/urgent care center/hospital for DM or heart problems, and co-payment, deductibles, and other out-of-pocket expenses for DM or heart problems during the study period. Occurrences of healthcare utilization will be valued using the average cost in the Medical Expenditure Panel Survey for similar patients [79].

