## Objectives {7}

We hypothesize that the combined intervention will improve both patient adherence and clinical outcomes over 12 months. We will randomize 17 teams in 12 FQHCs, recruiting 378 adults with T2DM to either (1) Office-GAP + Texting or (2) Texting only. Our primary outcome is medication adherence measured using eCAP electronic monitoring and self-report. Secondary outcomes are (a) diabetes-specific 5-year CVD risk as measured with the UK Prospective Diabetes Study (UKPDS) Engine score, (b) provider engagement as measured by the CollaboRATE Shared-Decision Making measure, and (c) patient activation as measured by the Patient Activation Measure (PAM).Aim 1: Compare the effects of Office-GAP + Texting intervention (group 1) with Texting only (controlling for attention) (group 2) in improving medication adherence, UKPDS risk score, provider engagement, and patients’ activation scores. Hypotheses:H1: Group 1 patients will show significant improvement compared with group 2 at 6 and 12 months in the (a) primary outcome of medication adherence, (b) secondary outcomes of UKPDS score, (c) provider engagement, and (d) patient activation scores.Aim 2: Identify barriers and facilitators to adoption, implementation, maintenance, and spread using an integrated RE-AIM and Consolidated Framework for Implementation Research (CFIR) and to explore potential mediators and moderators of effectiveness.Exploratory aim 3: Determine whether there are differences in cost and health care utilization between groups 1 and 2 using the Micro-Costing Questionnaire and The Health Services Utilization Form.

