#### Intervention description {11a}

Patients in either the intervention or control group will receive medical treatment-as-usual from the participating clinics, consisting of diabetes care, usual preventive care, and other medical treatment as needed (Table 1).

**Table 1 Tab1:** Intervention components

	Physician and staff education model for all intervention groups	
	GROUP 1 PAI + Texting	GROUP 2 Texting only
**Baseline visit**	**Group visit** **• Office-GAP PAI** **• Way2Health Texting program** **• BP Check** **• Surveys and checklist use**	**Group visit** **• Way2Health Texting program Only** **• BP Check** **• Complete Surveys**
**PAI (group 1)**	**• Baseline evaluation and patients complete all study questionnaires** **• Introduction to CVD/DM and lifestyle changes** **• Discussion of benefits of using each cardiac/diabetes medication** **• Discussion of goal setting, shared decision-making, and patient engagement** **• Review of patients’ medications and completion of the** ***Office-GAP agreement*** **• Review of ACP Booklet** ***Living with Diabetes & Medication Adherence video*** **• Pre and post evaluation of the group visit**	
**Texting (Care4Life) (groups 1 and 2)**	**•** ***Medication Adherence Intervention*****:** **Way2Health sends educational messages and quizzes on medication and adherence** **User responds to quiz** **•** ***DM Self-Management*** **Way2Health sends educational messages and quizzes on DM self-management** **User responds to quiz** **•** ***Blood Sugar Control Intervention*** **Way2Health sends educational messages about healthy blood sugar** **Way2Health sends blood sugar testing reminders** **User enters blood sugar readings and receives feedback on goals** **•** ***Blood Pressure Control Intervention*** **Way2Health sends educational messages about healthy BP** **Way2Health sends reminders to check and record BP** **User enters BP readings and receives feedback on goals** **•** ***Appointment Attendance Intervention*** **Way2Health sends appointment reminders** **User confirms appointment or reschedules**	
**6 and 12 months**	**-PAI Decision checklist** **-BP Check** **-Review of texting use** **- Surveys and exit interviews**	**-BP Check** **- Review of Texting use** **-Follow-up surveys** **-Exit Interviews**

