#### Primary outcome

Medication adherence is defined by the adherence metric (ratio of the number of days in which a patient takes his/her medication as prescribed, to total number of days he/she is expected to take them in that period) [27, 28]. Since there is no ideal medication adherence measure, a multi-measure approach is often recommended in assessing medication adherence to maximize ecological validity [28]. A meta-analysis also showed that this approach, including using a self-report method, can increase sensitivity to non-adherence [28, 29]. The concomitant use of both objective and subjective measures will provide higher reliability and represents the most rigorous approach to assessing medication adherence [30]. We will measure medication adherence using the eCap electronic pill container: the most objective and valid method of assessing adherence [28, 31], and a self-reported adherence measures described below. eCap will record the number of times the pill bottle is opened daily, over the course of the study. As in other trials, patients will be given eCap to assess adherence to their most frequently taken CVD prevention medication (e.g., BP, blood sugar lowering or cholesterol-lowering medication) [32], as identified by the primary care physician (PCP). Studies have shown that adherence to one medication parallels adherence to others [33]. Any medications taken during emergency room visits or hospitalizations will be obtained from patient reports and chart abstraction of patient medical records to avoid erroneously penalizing patients when the eCap is not used. Such days will be removed from the denominator of the formula to compute adherence rates. Self-reported adherence will be assessed using Adherence to Refills and Medications Scale (ARMS) a 14-item scale with two subscales for taking medications as prescribed and refilling medications on schedule [34, 35].

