Cost analysis will provide estimates for the value of resources used by each patient [65]. The value of resources not directly related to patient interaction, such as training costs and non-labor costs, will be allocated evenly across the intervention groups. Direct medical costs include expenditures for medical services and products usually paid for by the health system and consumer, including intervention costs (group visits, Texting), cost of medical care outside the interventions (use of hospital, emergency room, urgent care, outpatient visits, and prescription medications), and IT support (text messaging support). Direct non-medical costs include time and transportation to and from clinic visits and care provided by family members. Total cost per group at the end of the study will be computed by summing the costs for each patient. Mean cost per group will be calculated by dividing the total cost by the number of patients in each group. Research costs will not be included. Cost analysis will consider the perspective of the health system (FQHCs) and the consumer (patient). For costs analyses, we will follow the guidelines of the International Society for Pharmacoeconomics and Outcomes Research (ISPOR) Task Force on Good RCT-CEA Research Practices and will use the sample size determined for primary outcome in Aim 1 for cost analyses [66, 67]. Unit of analysis will be the patient [68]. All costs will be discounted to the base year according to time elapsed since randomization [69]. Distribution of cost data will be examined, and the differences in costs between study groups will be tested accounting for the nesting of patients within team clusters. Generalized linear models for Poisson distribution, or zero-inflated Poisson or negative Binomial model for counts of different healthcare utilizations will be used to compare the groups. Each type of health service use (e.g., hospitalizations, emergency room visits) will be analyzed separately. Two-part models for expenditures will typically be adopted to account for zero-expenditure for some individuals [70].

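### Aim 3 plans to cost and compare medical use without restriction by cause, but its only named utilization form counts emergency, urgent-care and hospital visits that patients attribute to diabetes or heart problems

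*Protocol article*

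**What the plan says.** Objectives {7} sets exploratory Aim 3 as determining "differences in cost and health care utilization between groups 1 and 2 using the Micro-Costing Questionnaire and The Health Services Utilization Form".

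Under Statistical methods {20a}, the subsection on the Aim 3 outcomes counts among direct medical costs the "cost of medical care outside the interventions (use of hospital, emergency room, urgent care, outpatient visits, and prescription medications". It states no restriction by cause. Patient costs are summed to a total and a mean per group. For counts of use it says: "Each type of health service use (e.g., hospitalizations, emergency room visits) will be analyzed separately".

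The subsection on cost and healthcare utilization then describes the form. On the source of the counts: "It gathers self-reported number of times the patient visits a specialist". For acute care and patient-paid costs the scope is "emergency room/urgent care center/hospital for DM or heart problems, and co-payment, deductibles, and other out-of-pocket expenses for DM or heart problems". Reported occurrences are valued at average costs from a national expenditure survey. The Micro-Costing Questionnaire is described there as covering training, supplies, materials, technical support and overhead.

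Blinding {17a} states that neither participants nor researchers are blinded. In Table 1, the group 1 session includes "Introduction to CVD/DM and lifestyle changes" and a discussion of the benefits of each cardiac and diabetes medication. The group 2 session does not.

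**The concern.** The quantity to be analysed and the instrument that supplies it have different scopes. A visit that the patient does not regard as due to diabetes or the heart is not counted, so it adds nothing to the patient's cost or to the visit counts being compared. The Discussion and Strengths sections present cost-effectiveness as something this trial will evaluate, so an incomplete cost total bears on its stated conclusions.

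If the omission were equal in both arms, it would understate cost and discard events without favouring either arm. Equality is not assured. The patient assigns the cause, knows the allocation, and in group 1 has had additional teaching on these diseases and on the purpose of each drug. The same visit could be labelled differently in the two arms. A true difference in use for other reasons would also be invisible in the Aim 3 comparison.

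**Working it through.** **Scope, side by side**

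| Element | Aim 3 cost analysis text | Utilization form as described |
|---|---|---|
| Hospital, emergency, urgent care | Included, no cause stated | Diabetes or heart problems only |
| Patient-paid costs | Consumer perspective, no cause stated | Diabetes or heart problems only |
| Who assigns cause | Not applicable | The patient, by self-report |
| Check against records | None stated for this comparison | None stated |

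The other Aim 3 instrument cannot fill the gap, because it records costs not tied to a patient. Valuing visits at survey averages prices the visits that are reported and does not recover those never asked about.

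**Size**

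The protocol gives no visit rate, attribution share or power for this comparison, so there is no figure to reproduce. Everything below is an illustration on assumed inputs.

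*Undercount.* If diabetes or heart problems make up 20% to 40% of acute use, the form misses 60% to 80% of it.

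*Differential labelling.* Let both arms have the same true all-cause rate λ per patient-year, and let patients attribute shares q1 (group 1) and q2 (group 2) to diabetes or heart. The form then shows λq1 and λq2, with ratio q1/q2. With λ = 0.60, q2 = 0.30 and q1 = 0.40:
- group 2: 0.60 × 0.30 = 0.18
- group 1: 0.60 × 0.40 = 0.24
- apparent rate ratio: 0.24 / 0.18 = 1.33, with no true difference
- with the shares reversed: 0.18 / 0.24 = 0.75

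To see how often this would reach significance, take the 320 evaluable patients split 9:8 like the teams (169 and 151), one year each, and a two-sided 5% Wald test of the log rate ratio, with SE = √(1/(169·λq1) + 1/(151·λq2)). For the case above, SE = √(1/40.56 + 1/27.18) = 0.248 and z = 0.288 / 0.248 = 1.16, so about 21% of trials would be significant. Clustering and overdispersion are ignored.

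| Shares, group 2 vs group 1 | Apparent ratio | λ = 0.3 | λ = 0.6 | λ = 1.0 |
|---|---|---|---|---|
| 30% vs 40% | 1.33 | 13% | 21% | 32% |
| 40% vs 50% | 1.25 | 11% | 18% | 26% |
| 50% vs 60% | 1.20 | 10% | 15% | 22% |
| 40% vs 60% | 1.50 | 28% | 49% | 70% |

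*A real difference hidden.* Let a share s of use be for other causes, and let that use rise by a factor R in group 1 with diabetes/heart use unchanged. The all-cause ratio is 1 − s + sR, while the form shows 1.00. For s = 0.30 and R = 1.25 this is 0.70 + 0.375 = 1.075. For s = 0.70 and R = 1.50 it is 0.30 + 1.05 = 1.35.

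**The case against.** The best defence is that counting disease-related use is legitimate in a diabetes and cardiovascular trial and is less noisy than all-cause use. The form was tested in a prior trial and is not reproduced here, the article condenses it to a sentence, and that sentence could be read as fixing the scope of the cost analysis. Aim 3 is exploratory. This stands as a defence of the narrower measure. It does not remove the mismatch, because the analysis text would then have to state the narrower scope, and it does not.

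The attribution argument also has limits. Table 1 gives both arms educational messages and quizzes on medication, diabetes, blood sugar and blood pressure, and the description of the texting programme says diabetes modules continue for the rest of the 12 months. The contrast is extra teaching in group 1, not teaching against none. Whether labelling differs, and in which direction, cannot be derived from the protocol.

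A reader might infer three stronger points that the text does not support:
- **Harms of other kinds are lost to the trial.** They leave only the Aim 3 comparison. The sections on the data monitoring committee {21a} and adverse events {22} have the monitoring board review adverse events, and all of them, related or not, are reported annually.
- **The form is the only structured record of acute care.** Adverse event reporting and chart abstraction are separate routes.
- **The eCap denominator is affected.** For that purpose the primary outcome section says: "Any medications taken during emergency room visits or hospitalizations will be obtained from patient reports and chart abstraction of patient medical records". It sets no limit by cause and makes no link to this form.

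**Conclusion.** The concern holds as a mismatch between what Aim 3 says it will cost and compare and what its form collects. As described, the form cannot yield the stated medical cost, and the arm comparison rests on patients' unblinded attribution of cause. That part follows from the text and needs no assumption.

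The size is not known. The ratios of 1.20 to 1.50, and the significance rates of 10% to 70%, follow entirely from assumed visit rates and attribution shares, and they show only that modest labelling differences could matter. The consequence is confined to an exploratory aim. It is worth correcting because the remedy is cheap and the trial intends to draw cost conclusions.

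**What to change.** Have the form ask, in both arms and at the assessments already planned, for every emergency, urgent-care and hospital visit of any cause, with its date and stated reason, and for out-of-pocket expenses on the same basis. Check the reported visits against the charts that research assistants already abstract. Report all-cause counts and costs together with the diabetes/heart subset. Which of the two is called the main comparison is partly a matter of preference, as long as both are shown.

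If the form cannot be changed, reword the Aim 3 analysis text and limit its conclusions to patient-attributed, diabetes- and heart-related utilization and cost. If the form in use already asks about any cause, correct its description instead.

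The cost is a form revision, a notice to the ethics board and modest research assistant time for recording and checking. All-cause counts will be noisier than the subset, which is a reason to keep both. Visits reported before the change would carry the old restriction unless they can be completed from charts.

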### Interim analyses {21b}

There are no interim analyses planned.

### Methods for additional analyses (e.g., subgroup analyses) {20b}

#### Subgroup analyses

We explore which subgroups of patients have benefited from the intervention through a cautious search [80, 81] of covariate patterns that contribute to “large” individual treatment effects. Statistical inference is not proposed. Using interaction terms between patient characteristics and intervention indicators, we will assess their impact on outcomes PAM and MAI at 12 months. A formal test of the interaction is not expected to be significant, but the size of the interaction might inform heterogeneity of the intervention effect.

### Methods in analysis to handle protocol non-adherence and any statistical methods to handle missing data {20c}

#### Addressing missingness [82]

In linear and nonlinear mixed models, likelihood-based inference using only the non-missing responses is valid under missing at random (MAR). Missing completely at random is likely to be untenable in our context. Techniques such as inverse-probability weighting will be used to accommodate missing data patterns that are neither MCAR nor MAR [83–85], an approach that we used in analyzing longitudinal censored medical costs data [85, 86].

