Hence the net difference (DID) at 12 month is *β*_32_. Our study is powered to test the hypotheses: (a) *H*_0_ : *β*_31_ = 0, (b) *H*_0_ : *β*_32_ = 0and jointly (c) *H*_0_ : (*β*_31_, *β*_32_) = 0. Two other design features are a serial correlation *ρ*_*W*_ between repeated measures over time, an intra-class correlation (ICC) *ρ* for clustering within practice team. We obtained plausible inputs for *r* and *ρ* from the literature and our own experiences [45–48]. In community intervention studies *ρ* is small (we use 0.002) but *ρ*_*W*_ is much larger (we use 0.30). The hypothesized adherence rates at 0, 6, and 12 months are 0.40, 0.42, and 0.42 in group 2 and projected to be 0.40, 0.62, and 0.65 in group 1. With 9 teams in the combined intervention group, 8 in the text alone group, and at least 22 patients in each team, the power to detect differences between groups at 6 months and 12 months is 80.8% and 90.4%, respectively. The power to detect the DID at 6 months is 71.4% and 83.1% at 12 months. Thus, our target sample size is a total of 320 patients. Because some attrition is expected over the 4-year period, we will recruit a total of 378 patients to account for attrition of 10% in YR=1, another 4% in YR=2, and another 2% in YR=3.

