## Statistical methods

### Statistical methods for primary and secondary outcomes {20a}

#### Statistical analysis

Medication adherence will be assessed in individual patients by eCAP monitoring. Hypotheses will be tested at 6 months and 12 months.Tests are two-tailed at 5% level of significance. We compare group 1 patients to group 2 patients at baseline using, as appropriate, ANOVA-F-tests, chi-square tests, and non-parametric tests to assess equivalence of potentially confounding physiological and contextual patient characteristics. If substantive differences are found, they will be adjusted for in subsequent analyses by regression techniques, guided by the degree of dissimilarity rather than strict statistical significance [63]. Equivalence between the groups will be assessed on age, gender, education, race/ethnicity, use of statins, b-blockers, aspirin, and ACE1/ARB, blood sugar and lipid values, and team factors such physician experience.

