##### Patient Activation Measure (PAM)

PAM is a continuous score on a 0–100 scale. Higher scores are associated with better activation [71, 72]. For MAI as continuous response, the beta regression model [73] with logit link posits the conditional mean and variance where *f*<1 is the under-dispersion. For PAM as continuous response, we will use a linear mixed model with mean and variance. Methods for the UKPDS risk score and patient engagement are entirely analogous. The structural forms of and are elicited from preliminary analyses of residuals [64]. Estimation of model parameters is via full maximum likelihood (ML), quasi-ML or restricted ML [64].

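### Inverse-probability weighting is assigned to data missing not at random, but weights estimated from observed data are valid only under MAR

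*Protocol article*

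**What the plan says.** The relevant text is the short section on addressing missingness under item {20c} of the protocol article. It makes three statements:

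- Mixed models fitted by likelihood to the observed responses give valid inference when data are MAR.
- On MCAR: "Missing completely at random is likely to be untenable in our context".
- On what lies beyond MAR: "Techniques such as inverse-probability weighting will be used to accommodate missing data patterns that are neither MCAR nor MAR". The authors describe this as "an approach that we used in analyzing longitudinal censored medical costs data".

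The article gives no weight model, no weights that depend on the unseen outcome, and no sensitivity parameter. It names no other technique for missing outcomes.

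On estimation, the PAM section says: "Estimation of model parameters is via full maximum likelihood (ML), quasi-ML or restricted ML". On expected loss, the sample size section says: "we will recruit a total of 378 patients to account for attrition of 10% in YR=1, another 4% in YR=2, and another 2% in YR=3". The evaluable target is 320.

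**The concern.** A pattern that is neither MCAR nor MAR is MNAR: the chance that a value is missing depends on the value itself, even after conditioning on what was observed. Standard inverse-probability weighting models the chance of being observed from recorded data and gives more weight to patients who resemble those lost. It removes bias only if nothing beyond the recorded data drives the loss, and that condition is MAR. The article therefore moves from a MAR method to a second MAR method and describes the second as covering MNAR.

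The article itself makes MNAR that differs by arm plausible for the adherence outcome:

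- Neither participants nor researchers are blinded (items {17a} and {17b}).
- The retention plan pays $50 in the control group and $100 in the intervention group at the 12-month visit.
- Research assistants upload the eCAP data (item {27}), so a patient who stops taking pills and stops attending may lose the very record that would show it.
- Disenrollment may follow if a caregiver takes over the medications (item {11b}).

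Observed history is also a weak guide. Baseline adherence is a proxy because eCAP data do not exist for that period. At the assumed serial correlation of 0.30, one earlier measurement explains about 0.30² = 9% of the variance of a later one.

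If the weighted and mixed-model results agreed, the article's wording would invite the conclusion that MNAR had been dealt with. The agreement would not support that.

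**Working it through.** **1. The plan's own figure.** Retention is 0.90 × 0.96 × 0.98 = 0.84672, and 320 / 0.84672 = 377.9, which rounds up to 378. The stated target is reproduced. Planned loss is (378 − 320) / 378 = 58 / 378 = 15.3%.

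**2. Size of a departure from MAR.** Let π be the proportion missing in an arm and δ the amount by which the missing patients' true mean adherence (the MAI, range 0 to 1) lies below what MAR predicts. The true difference is then lower than the MAR estimate by π₁δ₁ − π₂δ₂. The planned 12-month difference is 0.65 − 0.42 = 0.23. The values of δ are assumptions, since the article gives none. The 20% loss is an upper scenario, because the retention plan reports only that earlier studies kept more than 80%.

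| δ₁ (group 1 only, δ₂ = 0) | Loss 15.3% | Loss 20% |
|---|---|---|
| 0.10 | 0.015 (7% of 0.23) | 0.020 (9%) |
| 0.20 | 0.031 (13%) | 0.040 (17%) |
| 0.30 | 0.046 (20%) | 0.060 (26%) |

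If only group 2 is affected, the sign reverses. If loss and deficit are equal in both arms, the terms cancel: 0.153 × 0.20 − 0.153 × 0.20 = 0.

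**3. Does weighting pick this up?** A large-sample simulation (400,000 per arm) used the article's adherence means, a correlation of 0.30 and retention of 320/378. The following were assumed:

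- beta-distributed outcomes with precision 3;
- only 12-month adherence missing;
- a logit slope of response on adherence of 2 or 4;
- no clustering.

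Weights were fitted on baseline and 6-month values. The comparator was a MAR regression on the same two values, standing in for the mixed model. The true difference is 0.230.

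| What drives missingness | Weighted, slope 2 / 4 | MAR regression, slope 2 / 4 |
|---|---|---|
| 6-month value (MAR), one arm or both | 0.230 / 0.230 | 0.230 / 0.230 |
| Unseen 12-month value, group 1 only | 0.247 / 0.261 | 0.247 / 0.261 |
| Unseen 12-month value, group 2 only | 0.216 / 0.204 | 0.216 / 0.204 |
| Unseen 12-month value, both arms alike | 0.231 / 0.235 | 0.231 / 0.236 |

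Under MAR both methods recover the truth. Under MNAR in one arm both are biased by the same amount, 0.014 to 0.031 in absolute terms. Under the same MNAR mechanism in both arms the bias is small.

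**4. Can any weighting work?** When the weights included the unseen 12-month value, with its slope treated as known, the estimate returned to 0.230 to 0.231. That slope cannot be estimated from the observed data. It has to be supplied as a sensitivity parameter, and the article mentions none.

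**The case against.** A reader might infer that the trial has no analysis that tests its missing-data assumption. The documents do not support that. The statistical analysis plan is not shown and may contain a sensitivity analysis, and the article offers weighting as an example, not as the only technique. Nor can any analysis test MAR against MNAR from the observed data; departures can only be explored.

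It would also be too strong to say that every form of weighting needs MAR, as step 4 shows. The article cites sources for its approach that cannot be checked here, so a form with a sensitivity parameter may be intended. Still, the text describes no such form.

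The article does not call weighting a sensitivity analysis, and it does not say that weighted and unweighted results will be compared. Weighting also has a legitimate role: quasi-likelihood estimation, which the article allows, does not automatically share the MAR validity of full likelihood. This means that weighting need not be redundant, but it does not extend weighting to MNAR.

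Finally, the magnitudes rest on assumptions. The 0.20 deficit in one arm has no source in the article. Attrition is stated by study year while each patient is followed for 12 months, so 15.3% may not equal the share of missing 12-month outcomes. Even in that scenario 0.23 falls only to about 0.20, and no reversal of the conclusion is shown.

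All of this limits how far the point reaches. It leaves untouched the sentence that assigns a MAR method to MNAR data, which is an error in stated text and not a detail left to the analysis plan.

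**Conclusion.** The point stands in limited form. The only technique this article names for MNAR does not address MNAR in its standard form. It shares the MAR assumption of the likelihood model and additionally needs a correct weight model and positivity. Agreement between the two would say nothing about MNAR.

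The practical exposure is to missingness that differs by arm. It is moderate: about 0.03 of the planned 0.23 (13%), given 15.3% missing at 12 months and an assumed 0.20 deficit confined to group 1. It is close to nil if the same mechanism acts in both arms. These sizes are illustrations, not predictions. The text should be corrected before analysis.

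**What to change.** State that the likelihood analysis and the weighted analysis both assume MAR, and say what the weights condition on if weighting is kept.

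Replace weighting as the MNAR method by a sensitivity analysis that explores departures from MAR. Two suitable choices are:

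- delta-adjusted (pattern-mixture) multiple imputation, with shifts in MAI varied separately by arm until the conclusion changes;
- weights that include the unseen outcome, with a stated range for the sensitivity parameter.

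Shifts must be allowed to differ between arms, because equal shifts with equal loss largely cancel. The range should be fixed before outcome data are seen.

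The cost is a change of wording in the analysis plan and a short additional program. Recruitment and data collection are unaffected.
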